## Discussion

3

Stress urinary incontinence (SUI) is a highly prevalent condition imposing a substantial societal burden and significantly impairing the quality of life of affected women. Globally, the prevalence of urinary Incontinence in women exceeds 25%, and SUI constitutes the most prevalent subtype, accounting for more than half of all cases. Among Chinese adult women, the overall prevalence of SUI is 18.9%, with reported averages of 27.5% in urban areas and 32.5% in rural areas (2, 30). The prevalence of SUI increases with age, peaking in the 50–59 age group (28.2%) (31). Notably, mild and moderate SUI comprise approximately 90% of all cases (32), highlighting the large population that could benefit from effective nonsurgical interventions. SUI exerts multiple detrimental effects on patients' lives. Frequent urine leakage and the long-term reliance on protective pads severely disrupt daily activities, sleep, and social interactions.

Furthermore, the condition frequently precipitates psychological distress, including anxiety and depression (33). In addition to the personal suffering, SUI imposes a heavy economic burden on patients and healthcare systems. For instance, in the United States, the average annual treatment cost for SUI can be as high as $50,000 (34). Despite this significant economic impact, treatment-seeking rates remain low, with only about 8.2% of affected individuals receiving care (35). Given the global trend of population ageing, the prevalence of SUI is projected to rise, consequently escalating the associated social and economic burdens.

Normal function of the pelvic floor muscles and their supporting structures is crucial for maintaining continence, and impairment of this function plays a central role in the pathogenesis of SUI. The pelvic floor muscles are composed primarily of two fiber types: Type I (slow-twitch) fibers, which constitute approximately 70% and provide tonic, sustained support; and Type II (fast-twitch) fibers, comprising about 30%, which are responsible for phasic, rapid contractions during sudden increases in intra-abdominal pressure (36). During a sudden rise in intra-abdominal pressure, the Type II fibers of the levator ani muscle and the external urethral sphincter contract rapidly. This reflex contraction elevates the pelvic diaphragm, reduces the urethral curvature, and increases urethral closure pressure, thereby preventing urine leakage (4, 37). In patients with SUI, weakened pelvic floor muscles and diminished supportive function compromise the ability to counteract sudden rises in intra-abdominal pressure, resulting in involuntary urine leakage (4). Studies have demonstrated that compared to healthy individuals, the pelvic floor muscles in SUI patients exhibit reduced activation, diminished maximal voluntary contraction strength, and impaired endurance during sustained contractions (38). Histopathological findings in SUI include decreased muscle fiber density, disorganized arrangement, significant atrophy, a reduced proportion of Type II fibers, and fibrous replacement in the levator ani muscle (39).

The amplitude of the signal obtained from surface electromyography (sEMG) of the pelvic floor muscles reflects the number of activated motor units. Thus, sEMG can be used to assess the contractile function of both Type I and Type II muscle fibers across the different phases of the Glazer assessment protocol in patients with SUI. The sEMG signal parameters correlate well with the intensity of pelvic floor muscle contractions and serve as an indirect measure of muscle strength. The average peak amplitude during both fast (phasic) and endurance (tonic) contractions is significantly lower in SUI patients than in healthy controls, indicating functional impairment of both Type I and Type II muscle fibers (40, 41).

Pelvic floor ultrasound, conversely, provides a direct assessment of structural changes in the pelvic floor, such as hypermobility of the bladder neck and proximal urethra. This imaging modality offers high practicality, providing reliable, reproducible, and accurate measurements. Key sonographic metrics include bladder neck descent (BND), urethral rotation angle (URA), retrovesical angle (RVA), the position of the lowest point of the bladder (BN-S), urethral funneling, cystocele, and the levator hiatal area (42). In SUI patients, the thickness of the puborectalis muscle is reduced both at rest and during maximal voluntary contraction. During a pelvic muscle contraction, the levator hiatal area often demonstrates inadequate closure, and bladder neck mobility increases, alongside urethrovesical angle alterations. These sonographic findings are consistent with diminished muscle elasticity and contractile function, compromising the ability to maintain adequate urethral closure pressure during stress (42–44).

Acupuncture has a long history of use in treating SUI. A standard treatment protocol has been established in contemporary clinical practice, primarily involving acupoints in the lower abdomen [e.g., Zhongji (RN3) and Guanyuan (RN4)] and the sacrococcygeal region [e.g., Huiyang (BL35) and Zhongliao (BL33)] (7, 8).In clinical practice, lower abdominal acupoints, particularly RN3 and RN4, are among the most frequently selected (9). Our team's previous pilot work demonstrated that electroacupuncture stimulation at RN3 can induce immediate improvements in pelvic floor structure among SUI patients, including reduced bladder neck descent (BND), changes in the urethral rotation and retrovesical angles at rest and during Valsalva, and elevation of the lowest point of the bladder (45). These findings suggest that electroacupuncture at lower abdominal acupoints may exert a positive regulatory effect on the pelvic floor support system, influencing its functional and structural properties.

Despite established efficacy, the mechanistic understanding of electroacupuncture in SUI remains incomplete. For instance, the landmark study by Liu et al. (7) provided high-level evidence for the efficacy of electroacupuncture in SUI, demonstrating its superiority over sham acupuncture in reducing urine leakage and improving quality of life. However, that study relied primarily on clinical efficacy indicators such as symptom questionnaires and pad tests, failing to reveal the accompanying changes in pelvic floor function and structure underlying the therapeutic effects. Furthermore, many current clinical studies tend to combine electroacupuncture with pelvic floor muscle training (PFMT) as a complex intervention for SUI (8, 16). While these studies confirm the effectiveness of the combined therapy, the comprehensive nature of the intervention makes it difficult to distinguish the specific contribution of electroacupuncture from that of PFMT, particularly obscuring the exact impact of electroacupuncture alone on pelvic floor muscle function. Our team's previous pilot studies (10, 45)preliminarily found that electroacupuncture could immediately improve ultrasound parameters like bladder neck mobility, suggesting its potential mechanism of action via regulating pelvic floor support structures. However, these studies focused on the immediate effect of single acupoint stimulation and lacked long-term observation, limiting the strength of the evidence. Additionally, most mechanistic studies of electroacupuncture for SUI remain at the animal experiment stage (11, 14, 15), and there is a lack of systematic evaluation integrating its physiological effects in humans, combining symptomatology, pelvic floor muscle electromyographic activity, and morphological changes.

To bridge this critical gap, namely, the lack of a systematic evaluation integrating subjective symptoms with objective physiological and structural measures, we designed this randomized, single-blind, sham-controlled trial in accordance with the SHARE guidelines (20) to rigorously assess the specific effects of EA. By employing a validated sham acupuncture device, this trial aims to isolate the specific therapeutic effects of electroacupuncture from non-specific effects, thereby enabling a comprehensive assessment of its efficacy, safety, and impact on pelvic floor function. However, a recognized limitation inherent to acupuncture trials, including this one, is the potential influence of non-specific effects, such as the placebo effect, patient expectations, and the therapeutic ritual. Although the sham acupuncture technique is designed to minimize placebo effects, the inability to blind the acupuncturists and the potential for patients to perceive differences in needle sensation between real and sham treatments remain essential potential sources of bias. To mitigate this risk, participants will receive interventions individually in separate rooms to prevent communication between them. Participants will be blinded to their group assignment to maintain objectivity.

Furthermore, concomitant pelvic floor muscle training is prohibited during the trial period to avoid confounding. If the trial demonstrates the superiority of electroacupuncture over sham treatment, the observed benefits may be attributed to mechanisms such as enhanced pelvic floor muscle tone, reduced muscle fatigue, and subsequent improvements in pelvic floor structure and continence function.

To quantitatively assess the success of blinding, we will use the Bang Blinding Index upon completion of the treatment period. Participants will be asked to guess their group assignment, and the results will be analyzed to determine the effectiveness of our blinding procedures. Successful blinding will help distinguish the specific effects of electroacupuncture from non-specific effects. Nevertheless, the inability to blind therapists and the potential for participants to discern treatment allocation remain inherent methodological limitations. These factors will be carefully considered when interpreting the trial results.

To minimize bias from participant dropout, we have preemptively developed comprehensive strategies, including offering flexible scheduling, allowing tolerant visit time windows, enhancing communication with participants, establishing an early warning system for dropouts, and strictly applying the intention-to-treat (ITT) principle in data analysis, combined with multiple imputation methods to handle missing data. Finally, for ethical considerations, participants can continue any pre-existing specialized SUI treatments; however, all such concomitant treatments will be meticulously recorded and considered as covariates in the statistical analysis to control for their potential confounding effects.

Several other limitations of this study should be acknowledged. First, the single-center design and recruitment of participants from a single institution may limit the sample representativeness and generalizability of the findings. Consequently, the external validity and generalizability of the conclusions may be limited and should be interpreted cautiously. Differences in healthcare settings and patient populations across regions may affect the widespread applicability of the findings. Although unified operator training was implemented to standardize the protocol, other single-center factors, such as the specific treatment environment and equipment, could introduce systematic bias. Second, although the sample size meets the basic requirements for the primary outcome, it is relatively modest compared to large multicenter trials (7). The relatively small sample size may reduce the statistical power for detecting significant effects in exploratory subgroup analyses and some secondary outcome measures. Third, as SUI is a chronic condition, understanding long-term outcomes is crucial. However, this study is limited to assessing short-term efficacy immediately post-intervention due to budgetary and logistical constraints. The lack of follow-up beyond 6 weeks precludes conclusions regarding the sustainability of treatment effects and the long-term efficacy of electroacupuncture. To address these limitations, future research should prioritize multicenter, large-sample randomized controlled trials that enroll more diverse populations and incorporate long-term follow-up (e.g., ≥6 months). Such studies are needed to comprehensively evaluate electroacupuncture's efficacy and sustainability for SUI and generate more robust evidence to guide its clinical application.

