## Introduction

1

Stress urinary incontinence (SUI) is a highly prevalent condition among adult women. The International Continence Society (ICS) defines SUI as the complaint of involuntary urine leakage upon effort or exertion, such as laughing, sneezing, or coughing (1). Epidemiological data indicate a high incidence of SUI. The median global prevalence of urinary Incontinence in women is 27.6% (range: 4.8%–58.4%), with SUI accounting for over 50% of cases (2). SUI severely impacts patients’ social activities, physical exercise, and sexual life, leading to psychological issues such as anxiety and depression, as well as social isolation. Consequently, it significantly reduces quality of life (3) and imposes a substantial economic burden on society. SUI is closely associated with impairments in pelvic floor structure and function. Patients often exhibit a weakened urethral mucosal seal, inadequate urethral sphincter and pelvic floor muscle strength, laxity of fascia and ligaments, and other functional or structural abnormalities of the pelvic floor. Insufficient pelvic floor support can lead to hypermobility of the bladder neck and proximal urethra. When abdominal pressure increases, bladder pressure may exceed urethral closure pressure, resulting in urine leakage (4).

Current treatment options for SUI primarily include behavioral interventions, pelvic floor muscle training (PFMT), biofeedback, pharmacotherapy, and surgery (5). PFMT is the first-line treatment for mild to moderate SUI; however, it requires patients to adhere to 3–6 months of training to achieve potential efficacy. It also demands professional guidance and supervision, which can challenge patient compliance (6). Electroacupuncture has gained recognition as a promising non-pharmacological treatment for SUI. Studies have demonstrated its efficacy in reducing urine leakage and improving quality of life (7, 8). Acupuncture at lower abdominal acupoints is widely employed in SUI treatment (9). Notably, it has been shown to immediately reduce the mobility of the bladder neck and proximal urethra, thereby improving pelvic floor function (10).

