The therapeutic mechanisms of electroacupuncture for SUI are considered to involve multiple pathways. Firstly, it may modulate spinal and central reflex arcs to enhance urethral sphincter control and improve pelvic floor muscle function (7, 11). Secondly, it is thought to promote local blood circulation and nutrient supply, thereby aiding in the recovery of muscle elasticity and strength (12, 13). Additionally, electroacupuncture may facilitate tissue repair by modulating collagen metabolism in pelvic supportive structures (14, 15). These multifaceted actions highlight its potential as a comprehensive therapy for SUI. Despite its established clinical efficacy, significant gaps remain in the objective characterization of EA's impact on pelvic floor physiology. Many prior studies lack a systematic integration of objective functional and structural assessments. Furthermore, when EA is combined with pelvic floor muscle training, the specific effects attributable to EA alone are often unclear (7, 16).

Therefore, this sham-controlled trial aims to rigorously evaluate the efficacy of EA as a monotherapy for SUI and to investigate its specific effects on pelvic floor muscle function and structure, thereby providing novel mechanistic insights.

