### Participant and consumer involvement

2.2

The inclusion criteria are as follows: diagnosis of mild or moderate SUI in women (18, 19); age between 40 and 75 years. All participants will provide written informed consent before enrollment. Exclusion criteria include: urge urinary Incontinence, mixed urinary Incontinence, or overflow urinary Incontinence; history of surgical treatment for urinary Incontinence or pelvic floor surgery; genital prolapse of stage II or greater; symptomatic urinary tract infection; postvoid residual urine volume > 30 mL; maximum urinary flow rate < 20 mL/s; inability or limited ability to walk, climb stairs, or run; continuous use of medications affecting bladder function or ongoing specialized treatment for SUI; severe cardiac, cerebral, hepatic, renal, hematopoietic system, or psychiatric diseases; diabetes mellitus, multiple system atrophy, cauda equina lesions, or spinal cord pathologies; pregnancy, lactation, or intention to become pregnant during the trial period; presence of a cardiac pacemaker, metal allergy, or severe needle phobia. The withdrawal criteria are as follows: experience of severe complications or other serious illnesses that preclude continued participation; participant's request to withdraw from the trial. Data will be analyzed according to the intention-to-treat (ITT) principle.

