#### Statistical methods

2.6.4

Statistical analyses will be performed on the intention-to-treat (ITT) population and the per-protocol (PP) population. For the ITT analysis, missing data will be handled using multiple imputation by chained equations (MICE). All statistical analyses will be conducted using SPSS software (version 26.0; IBM Corp.). Results will be presented with 95% confidence intervals, and a two-sided *P* value of less than 0.05 will be considered statistically significant. Continuous variables normally distributed will be summarized as mean ± standard deviation, while those with a non-normal distribution will be summarized as median and interquartile range (IQR). Comparisons of continuous variables between the two groups will be performed using the independent samples *t*-test (for normal data) or the Mann–Whitney *U*-test (for non-normal data). Categorical data will be described as frequencies and percentages, and comparisons between groups will be made using the appropriate Chi-squared test or Fisher's exact test. For longitudinal analysis of outcomes measured over time, generalized estimating equations (GEE) or linear mixed-effects models will be employed to account for correlations within subjects and to examine time-by-group interaction effects. In secondary analyses, we will explore potential effect modification by menopausal status by including an interaction term in our statistical models. For the exploratory secondary outcomes, interpretation will focus on effect sizes and confidence intervals rather than unadjusted *P* values to avoid inflation of type I error due to multiple comparisons. No formal multiplicity adjustment will be applied to secondary endpoints.

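### Eligibility excludes women on ongoing specialised SUI treatment, but the Discussion lets participants continue it and adjusts for it; the rules conflict and leave the monotherapy question unsettled

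*Protocol article*

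**What the plan says.** Five places in the protocol article bear on this point.

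- **Section 2.2, Participant and consumer involvement.** The exclusion list contains "continuous use of medications affecting bladder function or ongoing specialized treatment for SUI".
- **Section 3, Discussion (paragraph on dropout and ethics).** It states that "participants can continue any pre-existing specialized SUI treatments; however, all such concomitant treatments will be meticulously recorded and considered as covariates". The reason it gives for the covariates is control of confounding.
- **Section 3, Discussion (earlier paragraph on design).** It states that "concomitant pelvic floor muscle training is prohibited during the trial period to avoid confounding".
- **Section 1, Introduction.** The trial "aims to rigorously evaluate the efficacy of EA as a monotherapy for SUI". The same section says that "PFMT is the first-line treatment for mild to moderate SUI".
- **Section 2.6.4, Statistical methods.** "Comparisons of continuous variables between the two groups will be performed using the independent samples" *t*-test, or the Mann–Whitney test for non-normal data. Generalized estimating equations (GEE) or linear mixed models are planned for outcomes measured over time. Menopausal status is the only additional model term named; concomitant treatment is not mentioned.

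**The concern.** A woman who is receiving specialised SUI treatment at screening is ineligible under Section 2.2 and may carry on with that treatment under the Discussion. Staff who follow one section will enrol a different population from staff who follow the other.

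The conflict reaches the research question. The Introduction criticises earlier trials because EA was combined with other treatment and its own contribution could not be separated. If background SUI treatment continues in this trial, the comparison becomes EA plus background care against sham plus background care. That is a legitimate question, but it is not the one stated.

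The analysis sentence adds a second problem. It calls the treatments concomitant, says they will be recorded, and makes them covariates, without saying at what time the covariate is measured. Status fixed before randomisation and use during the six weeks are very different things to put in a model. The reason given, control of confounding, does not settle which is meant: in a randomised comparison a baseline factor is not a confounder beyond chance imbalance.

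**Working it through.** **1. Planning figures.** Section 2.6.1 gives means of 8.59 g and 4.81 g (difference 3.78 g), SD 4.76 g, two-sided alpha 0.05 and power 80%. Then n = 2 × (1.96 + 0.84)² × 4.76² / 3.78² = 24.86, so 25 per group; 25 / (1 − 0.20) = 31.25, so 32 per group and 64 in total. The stated sample size reproduces and is not disputed here.

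**2. The two rules side by side.** A treatment can be continued only if it is ongoing at entry, so both sentences concern the same women.
- If Section 2.2 governs, no participant enters on such treatment. The permission has no one to apply to and the covariate is zero for everyone.
- If the Discussion governs, women on such treatment are admitted and the exclusion is not enforced.

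There is no reading under which both operate, and nothing else in the article resolves it.

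**3. Against the aim.** The first branch is compatible with the monotherapy aim. The second estimates EA added to whatever background care the women bring.

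**4. Against the training ban.** The Introduction names pelvic floor muscle training as the first-line treatment at the enrolled severity, and the Discussion prohibits it during the trial. A permission to continue *any* pre-existing specialised treatment would, read literally, include it.

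**5. When adjustment matters.** The document gives no uptake, no effect of co-treatment and no link between use and response, so the inputs below are assumptions. They show only under what conditions bias arises. Assumed: true EA effect 3.78 g and co-treatment adding 2 g to the reduction, with least-squares fits to 2,000,000 simulated women.

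| Case | Unadjusted (g) | Adjusted (g) |
|---|---|---|
| (a) Use fixed before randomisation, 20% of women | 3.78 | 3.78 |
| (b) On-trial use 10% EA, 30% sham, unrelated to prognosis | 3.38 | 3.78 |
| (c) As (b), but use tied to poor response (latent correlation 0.3 to 0.5) | 3.38 | 3.28 to 2.95 |
| (d) On-trial use 20% in both arms, tied to poor response (same correlations) | 3.78 | 3.78 |

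The unadjusted value in (b) and (c) is 3.78 + 2 × (0.10 − 0.30) = 3.38, the effect of assignment with co-treatment left as it falls. In (b), adjustment returns the effect with co-treatment held fixed, which is a different question. In (c) it returns neither: among women with the same co-treatment status, the EA women have the poorer prognosis, and the estimate falls below both 3.38 and 3.78. Bias therefore needs three things together: use measured after randomisation, use that differs by arm, and use related to response.

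**The case against.** The best defence is that the covariate is a baseline one. The Discussion speaks of pre-existing treatments, and *such* refers back to them. If so, status is fixed before randomisation and adjustment is harmless, as in case (a); if Section 2.2 governs instead, the covariate is empty. This largely stands, and it removes any claim that the plan as written is biased. What remains is narrow: the timing is not stated, and a woman may stop or change a pre-existing treatment during the trial, so *concomitant* and *recorded* could be coded as on-trial use.

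Three stronger readings are tempting and are not supported.

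- **That the adjusted estimate will be biased by a known amount.** One can build a scenario in which women with poor mid-trial response newly seek treatment, and obtain an adjusted difference of 3.29 g against 3.78 g, about −13%. But the Discussion sentence permits continuing treatment, not starting it, and the uptake threshold and correlation behind that figure are invented. Greater uptake in the sham arm does not follow from the text either.
- **That the planned tests rule out covariates.** The *t*-test and Mann–Whitney test take none, but Section 2.6.4 also plans GEE or mixed models, which do. Which model carries which covariate is commonly left to an analysis plan, and none is shown.
- **That the training ban flatly contradicts the permission.** A specific prohibition can be read as an exception to a general permission. The word *any* is loose, but this is weaker than the conflict with the exclusion.

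It may also be said that an article condenses a fuller protocol. That excuses omissions. Here two incompatible rules are both stated.

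**Conclusion.** The conflict between Section 2.2 and the Discussion is explicit and needs correcting. It decides who is enrolled and whether the trial can answer its monotherapy question. This conclusion rests on the wording alone and needs no numerical assumption.

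The covariate point is conditional. Adjusting for status at randomisation is harmless; adjusting for on-trial use could bias the difference under the three conditions shown. The document supplies nothing from which to size that risk, so no magnitude is claimed, and the figures in the table are not estimates for this trial.

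**What to change.** Reconcile the Introduction's aim, the exclusion in Section 2.2 and the two Discussion statements into one rule on concomitant SUI treatment, and say how pelvic floor muscle training falls under it. Which rule applies is for the sponsor's clinical team.

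- **If the exclusion stands:** delete the Discussion sentence that permits continuation and adjusts for it.
- **If such treatment is allowed:** amend the exclusion, and restate the aim as EA added to background care. Limit the covariate to use recorded before randomisation and name it in Section 2.6.4. Do not adjust the primary comparison for on-trial use. Keep all randomised women in the intention-to-treat analysis regardless of such use, and report use by arm.

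The cost is a few sentences of wording. No extra participants, visits or measurements are needed, since recording of concomitant treatment is already planned.
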